### Outcomes

2.6

#### Primary outcomes

2.6.1

The primary outcome measures of this study are coronary artery hemodynamic parameters and FAI assessed by CCTA. The coronary artery hemodynamic parameters include CT-FFR and WSS. These parameters will be evaluated at baseline and 24 weeks after randomization.

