**Results:**

As of July 2024, enrollment is complete, with trial completion expected in the first quarter of 2026. The primary outcomes are changes in CCTA-derived coronary hemodynamic parameters (CT-derived fractional flow reserve, wall shear stress) and fat attenuation index at 24 weeks. Secondary outcomes include imaging characteristics of plaques, traditional chinese medicine syndrome scores, seattle angina questionnaire scores, echocardiography, adverse cardiovascular events, and metabolomic profiles. Participants undergo follow-up at 4, 12 and 24 weeks post-randomization. All data will be collected in case report forms and analyzed according to predefined statistical plans.

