**Conclusion:**

This study will provide novel evidence on the efficacy and safety of SYF in improving coronary hemodynamics and reducing residual inflammatory risk in patients with SCAD and moderate stenosis, potentially offering a complementary therapeutic strategy.

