### Study design

2.1

This study is a randomized, double-blind, placebo-controlled superiority trial. It has been registered on the International Traditional Medicine Clinical Trial Registry Platform (registration number: ITMCTR2024000215) and approved by the Research Ethics Committee of Xiyuan Hospital, China Academy of Chinese Medical Sciences (approval number: 2024XLA060-2), confirming compliance with the Declaration of Helsinki, the 2020 Good Clinical Practice (GCP) guidelines for drug clinical trials, and the International Ethical Guidelines for Biomedical Research Involving Human Subjects (CIOMS). The decision to modify the protocol must be communicated by the Research Ethics Committee of Xiyuan Hospital, China Academy of Chinese Medical Sciences. The design of this study protocol follows the SPIRIT 2013 Statement (38, 39). The completed SPIRIT checklist is available in Supplementary File 3.

This study will be conducted at Xiyuan Hospital, China Academy of Chinese Medical Sciences, with a total of 60 participants to be recruited. After providing written informed consent, participants will be enrolled in the trial, which has a total treatment duration of 24 weeks, with follow-up visits scheduled at weeks 4, 12 and 24 of the intervention (Figure 1 and Table 1).

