(a)CT-FFR Assessment: CT-FFR was utilized as the core indicator of vascular function. The CT-FFR value was measured 2 cm distal to the stenotic lesion. For patients with multiple stenoses or multi-vessel involvement, the vessel with the most severe luminal stenosis and its most severe lesion were selected as the measurement point. The change before and after treatment was calculated (△CT-FFR = post-treatment − pre-treatment).(b)FAI Assessment: FAI was obtained to reflect the local inflammatory burden of the coronary artery. The FAI level was measured over a 10 mm length centered on the stenotic lesion. A higher value indicates more significant inflammatory infiltration of local adipose tissue. For patients with multiple stenoses, the most severe lesion was selected, and its change was dynamically tracked (△FAI = post-treatment − pre-treatment).(c)WSS Assessment: WSS reflects the frictional force exerted by blood flow on the vascular endothelium. WSS values were extracted at the most severe stenotic lesion. The change before and after intervention was tracked (△WSS = post-treatment − pre-treatment).(d)High-Risk Plaque Characterization: Based on the CAD-RADS™ 2.0 criteria (2), morphological instability features of the plaques were identified. A plaque must exhibit two or more of the following features to be classified as a high-risk plaque: ① Spotty calcification: Small, punctate calcified deposits observed within the plaque; ② Low-attenuation plaque: Non-calcified plaque areas with internal CT attenuation values below 30 HU; ③ Positive remodeling: The ratio of the outer vessel diameter at the plaque site to the average of the normal proximal and distal reference diameters is >1.1; ④ Napkin-ring sign: The simultaneous presence of two features on the cross-sectional image of a non-calcified plaque: a central low-attenuation core surrounded by a ring-like peripheral rim with higher CT attenuation.

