### Sample size

2.7

There are no studies using coronary artery hemodynamic parameters and FAI to evaluate the efficacy of traditional Chinese medicine in treating SCAD. This study is an exploratory trial and does not require sample size calculations (44). Sixty subjects will be recruited, with 30 participants allocated to each group, to investigate our research objectives.

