### Statistical analysis

2.9

According to the ITT analysis principle, the Full Analysis Set (FAS) is defined as the set of qualified cases that completed the study and analyzable drop-out cases, excluding excluded cases. The Per Protocol Set (PPS) is defined as the set of cases that comply with the trial protocol, have not concurrently used other drugs or treatments that may affect the trial results, have completed the full intervention and follow-up, and have completed the CRF as required. The Safe Set (SS) is defined as the set of cases that have received at least one dose of medication, possess baseline safety data, and have undergone at least one safety visit. Efficacy and safety will be evaluated based on the FAS, with the PPS used for sensitivity analysis.

Continuous variables will be described as mean ± standard deviation, categorical variables as frequency and percentage. Comparison of outcome measures between groups: continuous variables with a normal distribution will be analyzed using paired *t*-tests; those without a normal distribution will be analyzed using the Wilcoxon rank-sum test. Categorical variables will be compared using the *χ*^2^ test or Fisher's exact test. Subgroup analyses will be conducted based on whether patients have high-risk plaques (positive remodeling, low-attenuation plaque, spotty calcification, and napkin-ring sign) (2). Additionally, difficult-to-control and intergroup imbalanced confounding factors will be analyzed as covariates using analysis of covariance to eliminate their impact on efficacy evaluation. *P*-value <0.05 will be considered statistically significant. All statistical analyses will be performed using SPSS (version 25).

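### Three unranked primary outcomes share one unqualified P<0.05 threshold in a trial labelled both superiority and exploratory; if any one of them suffices, the false-positive risk is about 8–14%

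*Protocol article*

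**What the plan says.** - Section 2.6.1 (Primary outcomes): "The primary outcome measures of this study are coronary artery hemodynamic parameters and FAI assessed by CCTA". It adds: "The coronary artery hemodynamic parameters include CT-FFR and WSS". That makes three primary outcomes. The abstract's Results paragraph names the same three: "The primary outcomes are changes in CCTA-derived coronary hemodynamic parameters (CT-derived fractional flow reserve, wall shear stress) and fat attenuation index at 24 weeks".
- Section 2.6.4 (CCTA acquisition and image analysis) defines a separate before-after change for each outcome, for example "FAI = post-treatment − pre-treatment". There is no composite and no ordering.
- Section 2.9 (Statistical analysis) sets one threshold for all comparisons: P "<0.05 will be considered statistically significant". It gives no alpha split, hierarchy or joint-success condition.
- Section 2.1 (Study design): "This study is a randomized, double-blind, placebo-controlled superiority trial".
- Section 2.7 (Sample size): "This study is an exploratory trial and does not require sample size calculations". It sets 60 participants, 30 per group.
- Abstract, Conclusion: "This study will provide novel evidence on the efficacy and safety of SYF in improving coronary hemodynamics".

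**The concern.** With three primary outcomes, each judged at 0.05, the meaning of a positive trial depends on a rule that the text does not fix. If one significant result is enough, the overall false-positive rate exceeds 5%. If all three are required, it does not. The article supports neither reading explicitly.

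The labels add to the problem. The exploratory label is used to justify having no sample size calculation, while the superiority label and the expected evidence on efficacy point towards a firmer conclusion. A reader of the final report could not tell whether a single P value of, say, 0.03 on WSS is a primary efficacy finding or a signal for a later trial.

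**Working it through.** **Inputs from the article.** Three primary outcomes (section 2.6.1); one 24-week change per participant for each (section 2.6.4); threshold 0.05 per test (section 2.9); 30 per group (section 2.7). The article states no family-wise error rate, effect size, standard deviation or power, so there is no figure of its own to reproduce.

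**Assumptions, none of them in the article.**
1. Tests are two-sided, and each between-group test holds its nominal level.
2. Any one significant outcome counts as primary success.
3. The three outcomes have a common correlation ρ once each is oriented so that benefit is positive. No correlation is given, so a range is shown.

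**Step 1: independent outcomes.** Either direction: 1 − 0.95³ = 1 − 0.8574 = 0.1426. Benefit direction only: 1 − 0.975³ = 1 − 0.9269 = 0.0731. The upper bound for any correlation is 3 × 0.05 = 0.15.

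**Step 2: correlated outcomes.** With c = 1.96, and φ and Φ the standard normal density and distribution function:

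- Either direction: 1 − ∫ φ(u) [Φ((c − √ρ·u)/√(1−ρ)) − Φ((−c − √ρ·u)/√(1−ρ))]³ du
- Benefit only: 1 − ∫ φ(u) [Φ((c − √ρ·u)/√(1−ρ))]³ du

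The last column repeats the either-direction formula with the critical value for 0.05/3 = 0.0167. That is the first Holm step, and it determines the family-wise error when no outcome has an effect.

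| ρ | Either direction, 0.05 each | Benefit only (nominal 2.5%) | Either direction, 0.0167 each |
|---|---|---|---|
| 0 | 14.3% | 7.3% | 4.9% |
| 0.3 | 13.6% | 6.8% | 4.8% |
| 0.5 | 12.5% | 6.3% | 4.5% |
| 0.7 | 10.9% | 5.5% | 3.9% |
| 0.8 | 9.8% | 4.9% | 3.5% |
| 0.9 | 8.4% | 4.2% | 3.0% |

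A simulation of two-sample t-tests with 30 per arm (100,000 null trials per setting) agrees: 14.3%, 13.6%, 12.7% and 10.9% at ρ = 0, 0.3, 0.5 and 0.7.

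**Step 3: the alternative rule.** If all three outcomes had to be significant at 0.05, a false claim would require every one of the tests to reject, so the error could not exceed 5%. The inflation therefore comes from the any-one rule, not simply from having three outcomes.

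**Step 4: the price of adjustment.** The effect detectable with 80% power, by the normal approximation, is (z for alpha + z for power) × √(2/30):

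- alpha 0.05: (1.960 + 0.842) × 0.2582 = 0.72 SD
- alpha 0.0167: (2.394 + 0.842) × 0.2582 = 0.84 SD

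The two-sample t-test gives 0.74 and 0.86 SD. Both pairs assume that all 30 per arm are analysed.

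**The case against.** Four arguments weigh against the point.

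- **The superiority label may only give the direction of the comparison.** A trial can look for a difference from placebo and still be exploratory, and an exploratory trial need not control family-wise error. A reader might infer that the trial claims confirmatory status. The article never uses that word, and its conclusion is partly hedged. This stands, and it lowers the severity. It does not settle how an unadjusted significant result on one primary outcome is to be read.
- **A multiplicity rule may be in the analysis plan, which is not shown.** The abstract refers to predefined statistical plans. So the point cannot be that such a rule does not exist, and rules for secondary outcomes or metabolomics are no part of it. What remains is what the article itself fixes: three unranked primaries, one unqualified threshold and two labels that pull apart.
- **The size is conditional.** A reader might take a figure such as 11–14% as the trial's actual error rate. The documents do not support that. No section says that one outcome suffices, and the hypothesis in the Introduction joins hemodynamics and inflammation with an *and*, which could be read as a joint requirement. The correlation is also unknown. All three measures come from the same scans and software and centre on the most severe lesion, so values above 0.7 cannot be excluded, and there the error falls below 11%.
- **Nothing shows an intention to choose the label after seeing the results.** A reader might suspect this. The article shows two labels side by side, which is an inconsistency and no more.

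**Conclusion.** The point holds as a conflict within the article that leaves the primary claim undefined. The text allows a primary efficacy statement from any one of three unadjusted tests, and its labels do not say whether such a statement is intended.

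If one significant outcome is enough, the chance of at least one false-positive primary result is about 8–14% two-sided over correlations from 0.9 to 0. In the benefit direction it is about 4–7%, against 2.5%. At every correlation in that range it stays above nominal. Under an all-three rule it would be at most 5%. Severity: should be fixed. It affects what the trial may conclude, but the article calls the trial exploratory and the remedy is wording.

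**What to change.** Choose one of the following before unblinding. Section 2.4 has the analysis run on data coded A/B, so two-sided P values will be visible before the code is broken. The choice is best recorded before that coded comparison is run.

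**(a) If an efficacy claim is intended.** Apply Holm at a family-wise two-sided 0.05 across the 24-week between-group comparisons of CT-FFR, WSS and FAI: smallest P against 0.0167, next against 0.025, last against 0.05, stopping at the first failure. Alternatively, name one outcome as primary and make the other two secondary. The cost of Holm is sensitivity: at the first step the effect detectable with 80% power rises from 0.74 to 0.86 SD with 30 per arm and no dropout. Naming one primary keeps 0.74 SD for that outcome but gives up primary status for the other two.

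**(b) If the trial is exploratory.** Use that label throughout. Either delete the word superiority from section 2.1 or state that it describes only the direction of the comparison. Report between-group differences with 95% confidence intervals for all three outcomes, draw no efficacy conclusion from unadjusted P values, and align the abstract's conclusion. The cost is a more modest claim.

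Either choice needs only changes of wording in the protocol and analysis plan, with no new participants or measurements.

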#### Secondary outcomes

2.6.2

The secondary outcome measures of this study include imaging features of plaques, Traditional Chinese Medicine Syndrome Score (TCMSS), the Seattle Angina Questionnaire (SAQ), echocardiography, adverse cardiovascular events, and metabolomic analysis.

The imaging features of plaques include plaque morphology, location, volume, degree of stenosis, and calcification score, all of which will be assessed at baseline and 24 weeks after randomization. Echocardiography and metabolomics analyses will be performed at baseline and 24 weeks after randomization; TCMSS and SAQ will be recorded at baseline and 4th, 12th, 24th weeks after randomization. Adverse cardiovascular events are defined as cardiac death, non-fatal myocardial infarction, coronary revascularization, stroke, severe angina pectoris, and hospitalization due to acute coronary syndrome, malignant arrhythmia, or heart failure occurring within 24 weeks after randomization, and will be recorded at any time following participant enrollment.

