#### Removal, dropout, and termination criteria

2.5.3

Participants will be excluded from the study if any of the following conditions are found after the study finishes: a. Participants don't meet the inclusion criteria or meet the exclusion criteria; b. Participants don't adhere to the medication regimen as specified in the study protocol; c. Participants have no post-treatment visit records; d. Participants used concomitant medications during the trial that may affect the evaluation of the efficacy and safety of SYF. Excluded cases should not be included in the efficacy analysis. However, the safety analysis should include those who have received at least one treatment and have at least one safety record.

If participants experience adverse events such as cardiac death, non-fatal myocardial infarction, acute heart failure, severe angina pectoris, severe arrhythmia, or coronary revascularization (PCI or CABG) during the study, or significant deviations occur during the intervention that hinder the evaluation of drug efficacy, participants will be withdrawn from the trial based on the clinical physician's judgment. Participants may voluntarily withdraw from the trial if they are dissatisfied with the efficacy, experience adverse reactions, plan to receive other treatments, or for other reasons leading to unwillingness to continue treatment. Participants who fail to complete the observation period specified in the trial will be considered dropout cases, regardless of the timing or reason. The reasons for dropout will be documented in the case report form (CRF) and included in the final data analysis.

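### For TCMSS and SAQ, scored at four visits, the stated single-value tests leave baseline adjustment, missing week-24 scores and the deciding visit unsettled

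*Protocol article*

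**What the plan says.** Section 2.6.2 (Secondary outcomes) and Table 1 agree on the schedule: "TCMSS and SAQ will be recorded at baseline and 4th, 12th, 24th weeks after randomization". That gives three post-baseline scores per patient on each scale. Imaging, echocardiography and metabolomics are taken only at baseline and week 24.

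Section 2.9 (Statistical analysis) gives one rule for comparing all continuous outcomes between groups:

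- Normal data: "continuous variables with a normal distribution will be analyzed using paired" t-tests.
- Non-normal data: "those without a normal distribution will be analyzed using the Wilcoxon rank-sum test".
- Covariates: "intergroup imbalanced confounding factors will be analyzed as covariates using analysis of covariance", together with factors that are difficult to control.
- Threshold: a P "value <0.05 will be considered statistically significant".

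The section names no longitudinal model and no key visit for TCMSS or SAQ. On patients who leave, section 2.5.3 says "Participants who fail to complete the observation period specified in the trial will be considered dropout cases", whatever the timing or reason, and the full analysis set keeps those dropouts who can be analysed. Section 2.7 states: "This study is an exploratory trial and does not require sample size calculations".

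**The concern.** A t-test or a rank-sum test takes one value per patient. Applied to a scale with a baseline and three follow-up scores, it leaves three matters open.

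1. **Baseline.** Adjustment for the baseline score is not committed to. ANCOVA enters only where a factor turns out imbalanced or hard to control.
2. **Missing week-24 scores.** A patient with scores at weeks 4 and 12 but none at week 24 contributes nothing to a week-24 test unless a value is imputed. Section 2.5.3 lets patients leave because they are dissatisfied with efficacy and provides for withdrawal after severe angina, so leaving may well depend on symptoms.
3. **Deciding visit.** Any of weeks 4, 12 and 24 could be presented as the result.

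TCMSS and SAQ are also the only efficacy scales with a week-12 value, the point at which the regimen moves to its second stage. Section 2.5.1 says that stage is meant to explore whether longer treatment brings further benefit. How the group difference moves from week 12 to week 24 is a treatment-by-visit question, and the stated tests have no such term.

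**Working it through.** The plan gives no power, SD or error-rate figure for these scales, so there is nothing of its own to reproduce. The check sizes each consequence.

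**Inputs from the protocol article:** three post-baseline visits (2.6.2, Table 1); 30 per arm (2.7: "Sixty subjects will be recruited, with 30 participants allocated to each group, to investigate our research objectives"); threshold 0.05 (2.9), taken as two-sided because sidedness is not stated.

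**Assumptions, none given in the document:** SD = 1; equal correlation ρ between any two visits, 0.5 to 0.7 (0.5 to 0.9 for the error rate); proportion missing at week 24, d = 0.15.

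**Step 1. Baseline adjustment.** Per-patient variance is 1 for the raw week-24 score, 2 − 2ρ for the change score and 1 − ρ² for ANCOVA on baseline.

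| ρ | Raw | Change | ANCOVA | Change ÷ ANCOVA | Raw ÷ ANCOVA |
|---|---|---|---|---|---|
| 0.5 | 1.00 | 1.00 | 0.75 | 1.33 | 1.33 |
| 0.7 | 1.00 | 0.60 | 0.51 | 1.18 | 1.96 |

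Section 2.6.4 defines change scores only for the imaging measures, so either the raw or the change column could apply to TCMSS and SAQ.

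**Step 2. Using weeks 4 and 12 as well.** Given baseline, the later visits correlate at r = ρ/(1 + ρ), which is 0.333 or 0.412. Weeks 4 and 12 then explain R² = 2r²/(1 + r) of the remaining week-24 variance, which is 0.167 or 0.240. The variance of completer ANCOVA relative to the all-visit model is 1/(1 − dR²):

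- ρ = 0.5: 1/(1 − 0.15 × 0.167) = 1.03
- ρ = 0.7: 1/(1 − 0.15 × 0.240) = 1.04

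Simulation with 30 per arm gave 1.01 and 1.05, so the gain is about 1% to 5%. Simulated standard errors at ρ = 0.5 with 15% missing at random were 0.282 SD (change score), 0.246 SD (completer ANCOVA) and 0.244 SD (all visits). Nearly all of the gain is in the first step.

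If baseline is left out of both analyses, R² is 0.333 or 0.576. With 10% to 20% dropout, the all-visit variance is then lower by dR², from 0.10 × 0.333 = 3% to 0.20 × 0.576 = 12%.

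**Step 3. Bias from informative dropout.** Here leaving before week 24 was made to depend on the week-12 score in opposite directions in the two arms, with base missingness of 15% and 20%. Completer ANCOVA was biased by 0.06 to 0.08 SD and the all-visit model by at most 0.005 SD. Stronger dependence gave 0.09 to 0.11 SD for completer ANCOVA. With equal correlations the change score is unbiased under this mechanism, so the bias belongs to the assumed pattern as much as to the method.

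**Step 4. Error rate if any visit may count.** For three independent tests: 1 − 0.95³ = 14.3%. For correlated tests (1,000,000 simulated draws each):

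| Correlation | Exchangeable | First-order autoregressive |
|---|---|---|
| 0.5 | 12.5% | 12.9% |
| 0.7 | 10.9% | 11.4% |
| 0.9 | 8.4% | 8.8% |

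The range is about 8% to 14% per scale, counting each scale as one score, against 5% for a single named visit.

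**The case against.** The strongest reply is that this is a condensed article. A longitudinal model, the key visit for a secondary scale and the handling of its missing values commonly sit in the statistical analysis plan, which is not shown. That would answer pure silence. It does not fully answer this point, because section 2.9 names the methods for continuous outcomes, and those methods fit four-visit data poorly.

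Three stronger readings are tempting, and the document supports none of them.

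- A reader might infer both that the week 4 and 12 data are wasted and that each scale gets three chances of significance. These are alternatives. If every visit is tested, the early data are used; if only week 24 is tested, there is one chance. The text does not say which.
- A reader might infer that early leavers are dropped. The full analysis set keeps dropouts who can be analysed, and how they are handled is not stated. What holds is that a week-24 test needs an imputed value to include them.
- A reader might credit the whole 1.33 to 1.18 variance factor to the extra visits. Step 2 shows that they add only 1% to 5%.

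It is also fair that a week-24 ANCOVA on baseline would be valid and nearly as precise, that the dropout pattern in step 3 is hypothetical, and that no confirmatory claim rests on these scales. All of this stands and limits the weight of the point.

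**Conclusion.** The point holds in limited form. The methods stated in section 2.9 are inferior for TCMSS and SAQ because they leave baseline adjustment, patients without a week-24 score and the deciding visit unsettled.

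The main measurable loss is the missing commitment to baseline adjustment: a variance factor of about 1.33 to 1.18 against a change-score test, at assumed correlations of 0.5 to 0.7. Protection against bias matters only if leaving depends on earlier scores. The 8% to 14% error rate applies only if any of the three visits may be claimed, which the document neither states nor rules out.

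These are secondary outcomes of a trial declared exploratory, so the impact is modest and the primary imaging outcomes are untouched. Naming a paired t-test for a comparison of two independent groups is a separate error in the same sentence and needs its own correction.

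**What to change.** Add one paragraph to section 2.9 before unblinding, and preferably before the dataset coded as groups A and B goes to the statistician:

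- Analyse TCMSS and SAQ with a repeated-measures mixed model, with weeks 4, 12 and 24 as outcomes and treatment, visit, treatment-by-visit and baseline score as fixed effects.
- Include all randomised patients with at least one post-baseline score.
- Name the week-24 treatment difference as the single inferential contrast for each scale.
- Report weeks 4 and 12 as estimates with confidence intervals.

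This population is wider than the full analysis set as worded, which leaves out cases removed under section 2.5.3, so the two statements need to be aligned.

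The cost is the paragraph and slightly more programming. No new visits or data are needed. Section 2.2.1 reports enrolment complete as of July 2025, so analysis wording is among the few things that can still be changed.
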